### Adverse events monitoring

Given the nature of the interventions (yoga and mindfulness-based practices), we anticipate minimal risk. However, we recognise the potential for minor adverse effects, such as muscle soreness, fatigue or temporary emotional discomfort. To safeguard participants, adverse events will be monitored throughout the study. At each session, participants will be asked to report any adverse experiences or discomforts. Serious adverse events, if they occur, will be reported immediately to the study’s ethics committee and addressed by the study team.

An adverse event log will be maintained, with a clear process for assessment, documentation and management of any adverse events. Participants will be informed of whom to contact should they experience any unexpected symptoms or issues related to the interventions. If an adverse event occurs, appropriate medical intervention will be sought, and the participant may be withdrawn from the study if necessary to ensure their health and safety.

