### Interventions

Participants will be randomly assigned to one of four intervention groups (see table 1).

**Table 1 T1:** Detailed intervention protocols and session schedules across study groups

Group	Intervention	Description	Duration/frequencies/sessions
Group A	Sphinx pose yoga therapy	Participants will engage in Sphinx pose yoga therapy, focusing on back extension poses. The programme follows a simplified protocol aimed at improving accessibility, adherence and safety, especially for high-risk occupational groups.^17^ Sessions include warm-up stretching, targeted back extension and cool-down, with a focus on minimalism to ensure clinical benefit.	Frequency: 3 times per week for 12 weeks
			Session duration: 40 min per session
			Total sessions: 36 sessionsTotal contact time: 24 hours
Group B	MBSR (mindfulness-based stress reduction)	Participants will engage in a structured MBSR programme, including mindfulness meditation, body scan exercises, gentle yoga-based movements and group discussions. The programme follows the standard 8-week MBSR curriculum, extended to 12 weeks to match the duration of other interventions.^31^ Participants will be encouraged to practise daily at home using guided recordings.	Frequency: 1 session per week for 12 weeks
			Session duration: 2 hours per session (weeks 1–8), 1 hour per session (weeks 9–12)
			Total sessions: 12 sessionsTotal contact time: 20 hours
Group C	Usual care	Participants will receive guidance based on The Back Book, which includes advice on remaining active, avoiding prolonged rest and using simple pain control methods like over-the-counter analgesics. The approach encourages low-impact exercises (eg, walking, swimming) and basic stress reduction strategies, such as relaxation and breathing techniques.	Frequency: As per individual need, based on standard care guidelines
			Duration: 12 weeks
			Total sessions: Minimal contact, no structured sessions

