Group D	Combined yoga and MBSR	Participants in Group D will receive a comprehensive, multimodal intervention consisting of full-dose Sphinx pose yoga therapy and a standardised mindfulness-based stress reduction (MBSR) programme. This design aims to evaluate the additive or synergistic benefits of combining two evidence-based approaches targeting both physical and psychological dimensions of chronic low back pain without compromising the integrity of either protocol. Sessions will be scheduled on non-consecutive days to minimise participant fatigue and optimise engagement.	Frequency: Yoga: three times/week MBSR: once a week Duration: Yoga: same as Group A MBSR: same as Group B Total sessions: 36+12=48Total contact time: 24+20=44 hours

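### The only scheduled adverse-event enquiry is tied to intervention sessions, so as written usual care is never actively asked and no arm is asked in weeks 13 to 24

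*Protocol article*

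**What the plan says.** The section Adverse events monitoring makes a general promise: "To safeguard participants, adverse events will be monitored throughout the study". The method follows directly: "At each session, participants will be asked to report any adverse experiences or discomforts". The section names three other elements: an adverse-event log with a process for handling events, immediate reporting of serious events to the ethics committee, and a contact route described as "Participants will be informed of whom to contact should they experience any unexpected symptoms or issues related to the interventions".

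Table 1, under Interventions, sets how many sessions each arm has:

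- Group A (yoga): "Total sessions: 36 sessionsTotal contact time: 24 hours"
- Group B (MBSR): "Total sessions: 12 sessionsTotal contact time: 20 hours"
- Group C (usual care): "Total sessions: Minimal contact, no structured sessions", with contact described as "Frequency: As per individual need, based on standard care guidelines"
- Group D (combined): "Total sessions: 36+12=48Total contact time: 24+20=44 hours"

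The Study timeline places intervention delivery in weeks 1 to 12. Under Outcome measures, all arms are assessed at weeks 0, 12 and 24. The article does not name those assessments as points at which adverse events are collected.

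**The concern.** When the enquiry is attached to the intervention, the chance that an event is found depends on the arm. Group C has no session at which the question can be put, so its solicited count is zero whatever its participants experience. They can have events: they have back pain and receive advice that covers exercise and over-the-counter analgesics. After week 12 the enquiry stops for everyone, although follow-up runs for another 12 weeks.

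At stake is the ordinary safety table of a four-arm trial. The article hopes to inform treatment protocols and guidelines, so readers will set benefit against harm. If events are counted as they arise from the stated procedure, usual care could look safer than the active arms because of ascertainment alone. Events that were never asked about cannot be recovered at the analysis stage.

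**Working it through.** **1. Session counts reproduced from Table 1.**

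- A: 3 per week × 12 weeks = 36 sessions; 36 × 40 min = 24 hours, as stated.
- B: 1 per week × 12 weeks = 12 sessions; 8 × 2 h + 4 × 1 h = 20 hours, as stated.
- C: no structured sessions = 0.
- D: 36 + 12 = 48 sessions; 24 + 20 = 44 hours, as stated.

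**2. Scheduled enquiries per participant under the stated rule.**

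| Period | A | B | C | D |
|---|---|---|---|---|
| Weeks 1–12 | 36 | 12 | 0 | 48 |
| Weeks 13–24 | 0 | 0 | 0 | 0 |

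These are scheduled maxima. A participant who misses a session also misses the enquiry. The promise of monitoring throughout the study and the enquiry at each session cannot both hold as active collection for Group C, or for any arm after week 12.

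**3. What this does to recorded events.** The article gives no event rate and no recall period, so both are assumptions here. Two limiting models bracket the effect. In each, the quantity shown is the expected share of participants with at least one solicited report by week 12.

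*Model 1: equal yield per enquiry.* Each enquiry has the same chance q of producing a report, however long the interval since the last one. Share = 1 − (1 − q)^m, with m = 36, 12, 0 and 48.

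| q | A | B | C | D |
|---|---|---|---|---|
| 1% | 30.4% | 11.4% | 0% | 38.3% |
| 2% | 51.7% | 21.5% | 0% | 62.1% |
| 5% | 84.2% | 46.0% | 0% | 91.5% |

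*Model 2: complete recall since the previous session.* Every arm has the same true weekly risk r, and each enquiry captures everything since the last. Asking more often then finds nothing extra. Share = 1 − (1 − r)^12 in A, B and D, and still 0 in C.

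| r | A | B | C | D |
|---|---|---|---|---|
| 1% | 11.4% | 11.4% | 0% | 11.4% |
| 2% | 21.5% | 21.5% | 0% | 21.5% |
| 5% | 46.0% | 46.0% | 0% | 46.0% |

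**4. Reading the two together.** The spread among A, B and D runs from none (Model 2) to large (Model 1), depending entirely on recall. The zero for usual care, and the absence of any solicited report in weeks 13 to 24, appear under both models and do not depend on q or r.

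**The case against.** *The article is condensed, and silence is not a rule.* The log, the contact route and serious-event reporting are not limited to the active arms. All arms attend at weeks 12 and 24, and nothing says that adverse events are not asked about there. This stands in part: spontaneous and serious events from any arm can reach the log, so it would be wrong to say that usual-care events go unrecorded. But the article does state a rule for active collection, and that rule does not reach Group C. The contact route is passive, and its wording refers to the interventions, which fits usual care poorly.

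*No harms comparison is planned.* This is correct. Safety is not among the listed outcomes, the Statistical analysis section names no harms analysis, and monitoring is presented as a safeguard. The consequence is conditional on someone tabulating events by arm, as trial reports normally do.

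*Worsening back pain is captured anyway.* Also correct. Pain intensity and the Oswestry score are primary outcomes, measured in all arms at weeks 12 and 24. The gap concerns other events, and the timing of events between assessments.

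*A stronger reading is tempting: that yoga must look riskier than MBSR, and the combined arm worst, because they are asked three and four times as often.* The documents do not support this as a certainty. Model 1 holds the yield per enquiry constant although yoga's intervals are about a third as long as MBSR's. At equal weekly risk that requires incomplete recall, or reports unrelated to the interval. With complete recall the three arms agree. More sessions also mean more real exposure to, for example, muscle soreness, so true harms may differ too. The right description is confounding, not a known direction and size.

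**Conclusion.** The point holds. As written, active adverse-event collection is 36, 12, 0 and 48 scheduled enquiries in Groups A, B, C and D, and none in any arm for 12 of the 24 weeks. A comparison of usual care with any active arm would be confounded with ascertainment whatever the true rates. Among the active arms a bias is possible, but its size cannot be fixed from the article: between zero and the Model 1 figures, depending on recall.

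This rests on taking the session enquiry as the only scheduled one, which is all the article states. If the full protocol already asks all arms at weeks 12 and 24, the remedy is to say so and to base comparisons on those answers. No primary or secondary outcome is affected and no formal harms test is planned, so this should be fixed but is not critical to the trial's main conclusions.

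**What to change.** Ask all four arms the same adverse-event questions, with a fixed recall period, at common calendar times through week 24. The minimum is the existing week-12 and week-24 assessments, which gives 2 enquiries in every arm in place of 36, 12, 0 and 48. Two visits cover the whole study only if each looks back 12 weeks (2 × 12 = 24). A shorter recall period needs additional common times, such as a brief monthly message or call.

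Base any between-arm safety summary on these common enquiries alone. Keep the session reports for immediate safety management and list them separately for A, B and D. Adding the two visits while still pooling session reports would not solve the problem: under Model 1 with q = 1% and two extra enquiries per arm, the shares are 31.7% (A), 13.1% (B), 2.0% (C) and 39.5% (D).

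The cost is a short form at each visit and fewer minor events remembered than with session-level asking, though the recall period is then the same in every arm. Answers may reveal the allocation, so the form is best self-completed or taken by someone other than the blinded outcome assessors.

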### Blinding

Although participants and intervention providers cannot be blinded due to the nature of the interventions, all outcome assessors will be blinded to group allocation. Assessors will not be involved in the intervention delivery and will collect and score outcome measures without knowledge of the participant’s group assignment. This is especially important given the use of subjective outcomes such as pain intensity and disability.

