### Outcome measures

Outcome measures will be assessed at baseline (week 0), at the end of the intervention (week 12) and 12 weeks after the intervention (week 24).

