### Study timeline

Baseline assessment and participant enrolment (week 0).Intervention delivery (1–12 weeks).First follow-up (at the end of the intervention—week 12).Second follow-up (12 weeks after the intervention—week 24).

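### The one stated active adverse event question is tied to sessions (36, 12, none scheduled and 48 by arm), so by-arm counts cannot be read as a harms comparison with usual care

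*Protocol article*

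**What the plan says.** The section "To safeguard participants, adverse events will be monitored throughout the study" comes from, Adverse events monitoring, gives participant safety as its purpose. It names one active question: "At each session, participants will be asked to report any adverse experiences or discomforts". It also provides an event log, immediate reporting of serious events to the ethics committee, and a route that depends on the participant making contact: "Participants will be informed of whom to contact should they experience any unexpected symptoms or issues related to the interventions".

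Table 1 (Interventions) sets the number of sessions: 36 in Group A, 12 in Group B and 48 in Group D. For Group C it states "Total sessions: Minimal contact, no structured sessions" and "Frequency: As per individual need, based on standard care guidelines". The Study timeline confines treatment to twelve weeks: "Intervention delivery (1–12 weeks".

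After baseline, all four arms share two assessments, "at the end of the intervention (week 12) and 12 weeks after the intervention (week 24". No adverse event question is stated for either. Harms are not listed among the primary or secondary outcomes, and the Statistical analysis section names no between-arm comparison of harms.

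**The concern.** The events this section anticipates are sore muscles, tiredness and passing emotional upset. These are mild, common and known only if the participant mentions them, so the number that reaches the log depends on how often somebody asks. Under the stated rule, the frequency of asking is set by the assigned arm.

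If the final report summarises adverse events by arm, an excess in A, B or D over C would have two explanations, true harm or more frequent asking, and the data could not separate them. The active arms are not comparable with each other either, since Group D is asked four times as often as Group B. With equal true harm, the tendency would be to make yoga and MBSR look worse than usual care. Nor would a low count in Group C show that usual care is free of harm: that arm is advised on exercise and over-the-counter analgesics, and no scheduled question would pick up their effects.

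**Working it through.** **Session counts reproduced from Table 1**

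- Group A: 3 per week × 12 weeks = 36 sessions; 36 × 40 min ÷ 60 = 24 hours, as stated.
- Group B: 1 per week × 12 weeks = 12 sessions; 8 × 2 h + 4 × 1 h = 20 hours, as stated.
- Group C: none scheduled.
- Group D: 36 + 12 = 48 sessions; 24 + 20 = 44 hours, as stated.

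**Scheduled prompts at full attendance**

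The question is put once per session, so prompts equal sessions. The number per arm, 55, is from the Sample size calculation section (44 ÷ 0.80 = 55).

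| | A | B | C | D | Total |
|---|---|---|---|---|---|
| Prompts per participant | 36 | 12 | 0 | 48 | |
| Per week, weeks 1–12 | 36/12 = 3 | 12/12 = 1 | 0 | 48/12 = 4 | |
| Per arm (× 55) | 1,980 | 660 | 0 | 2,640 | 5,280 |
| Share of all prompts | 37.5% | 12.5% | 0% | 50% | 100% |

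The zero for Group C means that no prompt is scheduled in the text. It does not mean that nobody in that arm could ever be asked. After week 12 the sessions have ended, so no active question is stated in any arm for weeks 13 to 24.

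**Do the other provisions even this out?**

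- The undertaking to monitor throughout the study names no method or visit.
- The contact route is open to every arm, but it is passive. It is worded around unexpected symptoms or problems arising from the interventions, so a usual-care participant with ordinary soreness has little reason to use it.
- Contact in Group C is driven by need. Any asking at those contacts would tend to follow symptoms and not a calendar. This is a reading of Table 1, which does not mention adverse event questions.
- The questionnaires given to all arms, including the BDI and GAD-7, are outcome measures and not adverse event capture.

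**Illustration under assumptions**

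The article gives nothing from which the resulting difference in recorded events can be derived. To show the mechanism only, assume equal true harm in all arms, a chance q that any one prompt elicits a complaint, a chance s of an unprompted report, and independent responses. With k prompts, the chance of at least one recorded event is 1 − (1 − s)(1 − q)^k. Taking s = 10%:

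| q (assumed) | A | B | C | D |
|---|---|---|---|---|
| 0.5% | 24.9% | 15.3% | 10.0% | 29.2% |
| 1% | 37.3% | 20.2% | 10.0% | 44.4% |
| 2% | 56.5% | 29.4% | 10.0% | 65.9% |

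The ordering follows from the schedule. The sizes rest wholly on q and s, which are not document figures, and should not be quoted as estimates.

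**The case against.** The strongest reply is that the plan never proposes the use being criticised. The section exists to protect participants, harms are not an outcome, and no test of harms is planned. For its stated purpose, asking at each exposure is sound. All of this stands, and it keeps the point minor.

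The second reply is that a condensed article may leave follow-up questions to the full protocol, and that asking at each session does not exclude asking elsewhere. It is true that the full protocol may contain a common question. But the article is not silent on timing: it states a rule, and that rule applied to its own Table 1 gives unequal asking. The general promise of monitoring does not alter this, because it attaches to no visit or question.

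Third, the prompt counts measure asking and not bias in recorded events. That is correct, and no size of bias is claimed.

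Fourth, a common question at weeks 12 and 24 relies on recall over up to twelve weeks. Participants know their treatment, and those asked up to 48 times may remember and attribute events differently. That also stands: the remedy gives a common basis for comparison but does not remove every source of unequal reporting.

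**Conclusion.** The point holds, as an optional improvement. Following the text as written, active adverse event questioning runs at 36, 12, none scheduled and 48 prompts per participant in A, B, C and D, with none stated in any arm after week 12. Counts gathered this way serve participant care but cannot support a statement about harms relative to usual care, or between the active arms.

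The figures assume full attendance and 55 participants per arm, and that no further question is set in a document not shown. The size of any distortion in recorded events cannot be derived from the article. Serious events are less affected, because their reporting is not tied to sessions. The sample size and the efficacy analysis are untouched.

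**What to change.** Keep the session question for participant care. In Adverse events monitoring, add that all four arms will answer one identically worded adverse event question at the existing week 12 and week 24 assessments. Use a short self-completed form that goes straight to the adverse event log and not to the outcome assessors. The Blinding section says that these assessors "will collect and score outcome measures without knowledge of the participant" having been identified by group, and an answer that mentions yoga or mindfulness would reveal it. State that any by-arm summary of harms will use this common question, and that events reported at sessions will be listed separately as descriptive.

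The cost is one or two sentences and a short form. Prompts on the common schedule become 2 per participant in every arm: 55 × 2 = 110 forms per arm and 220 × 2 = 440 in all. If 20% drop out before week 12, the total is 44 × 4 × 2 = 352. There are no extra visits and no added contact in the usual-care arm, and active questioning extends to Group C and to weeks 13 to 24. The drawback is that some minor events will be forgotten between visits.

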## Discussion

CLBP is a growing epidemic, particularly among HCPs, with prevalence estimates for nurses ranging from 50% to 80%.^23^ The biopsychosocial model of chronic pain highlights the complex interplay of biological, psychological and social factors in CLBP.^24^ Conventional treatments have shown limited effectiveness, with less than 50% of patients experiencing relief after 1 year.^25^ Non-pharmacological therapies like physical therapy, yoga and acupuncture offer moderate benefits at best.^26^ While opioids have been a common treatment, recent guidelines recommend limiting their use due to safety concerns.^26^ Novel approaches being explored include chemonucleolysis, platelet-rich plasma injections and stem cell therapies.^18^ Additionally, mind-body exercises such as yoga and tai chi show promise in addressing both physiological and psychological aspects of CLBP.^23^

Mindfulness-based interventions (MBIs) and yoga have shown promise in managing chronic pain. Studies indicate that these practices can reduce pain perception, improve mobility and enhance overall well-being.^27^ A systematic review of MBSR for CLBP revealed significant improvements in pain measures, quality of life and mental health compared with control groups.^28^ An experimental single-case study on meditation-based lifestyle modification, a yoga-based intervention, demonstrated positive effects on pain intensity, quality of life and pain self-efficacy in patients with chronic pain.^29^ Additionally, a review of yoga and other meditative movement therapies confirmed their efficacy in reducing chronic pain symptoms, emphasising the importance of professional instruction.^30^ These findings suggest that MBIs and yoga can be valuable components of multidisciplinary pain management strategies, potentially reducing reliance on pain medications. Building on this evidence, our previous randomised controlled trial demonstrated that yoga significantly improved psychophysiological biomarkers among healthcare professionals with CLBP.^17^ These results provide a strong foundation for the current study’s expanded scope.

This study is distinctive in its integration of both subjective and objective outcome measures to evaluate the efficacy of Sphinx pose yoga and MBSR in managing CLBP. Alongside traditional self-reported assessments of pain intensity, functional disability, quality of life, depression, anxiety and stress, the trial incorporates objective physiological markers such as cortisol, β-endorphins, substance-P, IL-6, CRP and HRV. By combining clinical and psychophysiological data, this approach provides a more comprehensive understanding of the mechanisms through which mind-body interventions influence chronic pain and overall well-being.

## Data Availability

Data are available upon reasonable request.
